### Secondary outcome

The secondary outcome will be the the intervention's effect on clinical care processes and outcomes associated with the care of patients with pre-eclampsia and eclampsia. These are based on a priori understanding of existing policies and on published eclampsia research,^(34)^ such as the PHOENIX trial.^(35)^ Selected clinical care processes and outcomes are: blood pressure monitoring, request of relevant laboratory investigations, time to administration of antihypertensives, time to intravenous administration, antihypertensive administration (in minutes), magnesium sulfate, volume of fluid administration, and the use of intravenous antihypertensives. In addition, outcomes for both the fetus^(35)^ (neonatal ICU admission, preterm birth, Apgar score, placental abruption, intrauterine fetal death (IUFD), intrauterine growth restriction (IUGR), mortality) and the mother^(34)^ (ICU admission, length of hospital stay, mortality, and neurological deficit) will also be assessed.

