#### Primary outcome

The individual components of Reach, Fidelity, and Adoption of the RE-AIM framework will be computed as percentages, as shown in table 1. To assess fidelity, a checklist of key clinical interventions will be developed from the protocol and compared to the care delivered. This will include the frequency of blood pressure monitoring, the threshold for administering intravenous antihypertensives, and the timeliness of magnesium sulfate administration. Fidelity, reach, and adoption will be equally weighted, so a composite computation will be done using the mean. A threshold of 80% in each of the three domains will define success.

**Table 1 t1:** Primary and secondary outcome variables

Outcome	Measure and reporting
Implementation (primary outcome)	Fidelity: proportion of patients who are correctly managed with the protocol Numerator: number of patients who are correctly managed with the protocol Denominator: number of patients diagnosed with pre-eclampsia with severe features and eclampsia
	Reach: the proportion of patients who get managed with the protocol Numerator: number of patients who get managed with the protocol Denominator: number of obstetric emergency patients who presented at the Emergency Unit with the diagnosis of pre-eclampsia with severe features and eclampsia
	Adoption: proportion of patients who get managed with the protocol 6 months after the implementation Numerator: number of patients who get who get managed with the protocol in the 6th month of implementation Denominator: number of eligible patients who present to the Emergency Unit
Intervention effect and patient safety (secondary outcomes)	**Maternal** Hospital length of stay (in days) ICU referral and admission (expressed as a %) Hospital mortality (expressed as a %) ICU mortality (expressed as a %) Time to antihypertensive administration (in minutes; defined as the time between admission at the Emergency Department and the time of first administration of antihypertensive) Time to intravenous antihypertensive administration (in minutes; defined as the time between the first recorded blood pressure ≥ 180/110mmHg and the time of first administration of intravenous antihypertensive) Daily volume of fluid administration (expressed in mL/day) Time to magnesium sulphate administration (in minutes; defined as the time between admission at the Emergency Department and the time of first administration of magnesium sulphate)

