	**Fetal** Neonatal ICU admission (expressed as a %) [Numerator = number of babies admitted to neonatal ICU, denominator = number of babies delivered] Preterm birth (expressed as a %) [Numerator = number of preterm deliveries, denominator = number of babies delivered] Placental abruption (expressed as a %) [Numerator = number of placental abruption, denominator = number of babies delivered] IUFD (expressed as a %) [Numerator = number of preterm intrauterine fetal deaths, denominator = number of babies delivered] IUGR (expressed as a %) [Numerator = number of IUGR, denominator = number of babies delivered] Average Apgar score at 1 and 5 minutes

ICU - intensive care unit; IUFD - intrauterine fetal death; IUGR - intrauterine growth restriction.

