#### Secondary outcomes

The secondary outcome variables will be measured in the pre-implementation, peri-implementation, and post-implementation periods. The details of the outcome variables have been listed in table 1. Changes in measure (i.e., time, therapy, event rate) will be reported descriptively. The study is not powered to detect a significant change associated with the intervention; rather, these clinical process and outcome measures will provide a signal for safety and provide important feasibility information to inform future scalable studies if the protocol and co-design approach to implementation is found to be effective.

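### Table 1 limits the IUFD numerator to preterm deaths and has no row for the fetal/neonatal mortality and maternal neurological deficit that the Secondary outcome section promises

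*Protocol article*

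**What the plan says.** The Secondary outcome section of the protocol article names the fetal outcomes, and its list ends "intrauterine fetal death (IUFD), intrauterine growth restriction (IUGR), mortality) and the mother". IUFD carries no gestational limit there, and mortality is a separate item. The maternal list reads "ICU admission, length of hospital stay, mortality, and neurological deficit) will also be assessed".

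The analysis plan, under Secondary outcomes, states: "The details of the outcome variables have been listed in table 1". The fetal block of Table 1 gives the IUFD rate as "Numerator = number of preterm intrauterine fetal deaths, denominator = number of babies delivered". That block ends with "Average Apgar score at 1 and 5 minutes" and has no mortality row. The only mortality rows in the table, hospital and ICU, stand under the maternal heading. No row covers neurological deficit.

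The same part of the analysis plan calls the comparisons descriptive and unpowered, and gives their purpose: "these clinical process and outcome measures will provide a signal for safety".

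**The concern.** Table 1 is the only place in the article that gives numerators and denominators for the fetal outcomes, and the analysis plan sends the reader there. An analyst who builds the report from it would leave intrauterine deaths at term out of the IUFD count while keeping term babies in the denominator. The same analyst would find no instruction for deaths after birth, or for neurological deficit in the mother.

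These measures are to be set side by side for the pre-, peri- and post-implementation periods as a safety signal. No formal test stands behind that signal, so its value rests on counting the events completely and in the same way in each period. Death of the baby is the most serious of the fetal outcomes, and it is the one defined most narrowly.

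**Working it through.** No sample size, power or alpha figure bears on this point, and the plan gives no IUFD rate to reproduce. The check is a comparison of the text with the table, followed by a short formula.

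**Step 1. Outcome lists side by side**

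| Named in the Secondary outcome section | Table 1 |
|---|---|
| Neonatal ICU admission | Row present |
| Preterm birth | Row present |
| Apgar score | Row present |
| Placental abruption | Row present |
| IUFD, no gestational limit | Row present, numerator preterm only |
| IUGR | Row present |
| Mortality (fetal list) | No row |
| Maternal ICU admission | Row present |
| Maternal length of hospital stay | Row present |
| Maternal mortality | Rows present (hospital and ICU) |
| Maternal neurological deficit | No row |

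Six of the seven fetal outcomes have a row, and one of those six is narrowed. Three of the four maternal outcomes have a row.

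**Step 2. Numerator against denominator**

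The IUFD denominator is all babies delivered, at term or before. The numerator admits only deaths before term. The two do not refer to the same population: a preterm-only numerator would call for a preterm denominator, and an all-births denominator calls for all intrauterine deaths.

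**Step 3. Effect on the reported level**

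Let D be all intrauterine deaths, N all babies delivered, R = D/N, and t the share of D that occurs at term. The Table 1 rate is then

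(1 - t) × D/N = (1 - t) × R.

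The documents give no t. Purely as an assumed range:

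- t = 0.1: the table reports 0.90 R
- t = 0.3: the table reports 0.70 R
- t = 0.5: the table reports 0.50 R

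**Step 4. Effect on the comparison between periods**

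Reported ratio, post to pre = [(1 - t_post) / (1 - t_pre)] × [R_post / R_pre].

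If t is the same in both periods, the ratio is undisturbed and only the level and the absolute difference shrink. If t moves, the ratio is distorted. With R unchanged and t going from an assumed 0.1 to 0.3, the reported ratio is 0.70/0.90 = 0.78, an apparent fall of 22% with no change in deaths. The reverse movement gives 0.90/0.70 = 1.29, an apparent rise of 29%.

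**Step 5. Deaths after birth**

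No fetal row counts them. Neonatal ICU admission and Apgar score may be related to them but do not count deaths. No proportion can be given, because the documents contain no counts.

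**The case against.** A reader might infer that term stillbirths and newborn deaths disappear from the study. The documents do not support that. The Secondary outcome section still says that unrestricted IUFD, fetal mortality and maternal neurological deficit will be assessed. The analysis plan says that the details are in Table 1, not that anything absent from it is dropped. The table and the text are loosely matched in other places too: blood pressure monitoring and laboratory requests are in the text but have no secondary-outcome row, and ICU mortality has its own row but is not named separately in the text. The Data collection section also describes a registry covering the neonatal ICU that is to supply outcomes for the cohort, so some newborn deaths may well be recorded. It would not cover babies who die elsewhere.

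A reader might also take the preterm limit for a deliberate analytic choice. It may be a slip. The row label and the table's abbreviation note carry no limit, the denominator fits an all-IUFD rate, a preterm birth row stands two rows above, and nothing else in the article suggests such a restriction.

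Finally, an article condenses, and the exact mortality window could sit in the full protocol.

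Most of this stands, and it limits the point to a contradiction between text and table on secondary, descriptive outcomes. It does not remove the point. Condensing can explain a missing row, but not a stated numerator that conflicts with the text. A slip in the one place that defines the measure still has to be corrected.

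**Conclusion.** The point holds as an inconsistency with a wrong operative definition. As written, the Table 1 IUFD rate contradicts the outcome in the Secondary outcome section, and two outcomes promised there have no definition in the table named as the source of details.

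The consequence is conditional. If Table 1 governs, intrauterine deaths at term are left out of the IUFD rate and newborn deaths have no defined measure. The level of the safety signal is then too low, and its change across periods can be distorted in either direction if the term share changes. The size cannot be derived from the documents: the factors 0.90, 0.70 and 0.50 above rest on assumed term shares and show only how the rate responds.

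The primary outcome (fidelity, reach and adoption) is unaffected, and no test, threshold or sample size depends on these measures. The correction should be made, but the point is not critical to the study.

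**What to change.** In Table 1:

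1. Delete the word preterm from the IUFD numerator, so that all intrauterine fetal deaths are counted over all babies delivered. If the restriction is intended, state the reason, use a preterm denominator to match, and align the Secondary outcome section.
2. Add a row for the mortality already named in the fetal list. Say whether it means fetal, neonatal or both, and give its numerator, denominator and time window.
3. Add a row for maternal neurological deficit, with its measure.

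The cost is a few lines of table wording and, where they are not already planned, a few fields on the electronic case report form. According to the Data collection section, that form is still to be developed and piloted. The fields should be in place before baseline collection starts, so that the same definitions apply in all three periods.

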### Study participants

The study will include all patients who present at the obstetric emergency with the clinical assessment of pre-eclampsia with severe features or eclampsia. Severe features are defined as the presence of one of the following; platelets, 100 x 109, severe persistent right upper quadrant pain, renal insufficiency (serum creatinine > 1.1mg/dL or doubling of serum creatinine in the absence of renal disease), pulmonary oedema, visual disturbance, unexplained new-onset headache unresponsive to medication and HELLP syndrome acronym from hemolysis, elevated liver enzymes and low platelets.^(13)^

Patients who present dead on arrival to the emergency unit will be excluded. There are a few patients who will not present to the ED with pre-eclampsia/eclampsia but may develop the condition days later during a hospital admission for another pregnancy-related condition. These patients will also be excluded, given the variation in their hospital journey and the likely limited number of affected patients.

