### Analysis plan

#### Patient demographics and patient characteristics

Descriptive statistics (mean/median) will be used to describe baseline patient characteristics: age, gravidity, parity, and blood pressure. The patient categories of antepartum and postpartum will be reported as percentages. The presenting diagnoses of the patients will also be reported as percentages.

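### Fetal death, placental abruption and growth restriction are counted without separating events present at arrival from later ones, so changes in these three rates cannot be attributed to the protocol

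*Protocol article*

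**What the plan says.** In the protocol article, Table 1 groups the fetal outcomes under "Intervention effect and patient safety (secondary outcomes". Three of them are plain counts over all babies delivered:

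- growth restriction: "IUGR (expressed as a %) [Numerator = number of IUGR, denominator = number of babies delivered";
- intrauterine fetal death: "IUFD (expressed as a %) [Numerator = number of preterm intrauterine fetal deaths, denominator = number of babies delivered";
- abruption: "Placental abruption (expressed as a %) [Numerator = number of placental abruption, denominator = number of babies delivered".

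None has a starting time, and none requires the fetus to be alive or free of the event at arrival. The time-to-treatment outcomes in the same table do have a starting point; one is "defined as the time between admission at the Emergency Department and the time of first administration of antihypertensive".

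The Study participants section admits women who already have severe features or eclampsia when they present. The section on patient characteristics names "baseline patient characteristics: age, gravidity, parity, and blood pressure". It also reports antepartum and postpartum categories and presenting diagnoses as percentages. It names neither gestational age nor fetal status at arrival, and the fetal rates are not split by antepartum or postpartum presentation.

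The Abstract says the secondary outcomes are compared with the pre-implementation period. The Secondary outcomes part of the analysis plan makes that comparison descriptive, states that the study lacks power for it, and uses the measures as a safety signal.

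**The concern.** Care under the protocol begins when the woman reaches the emergency unit with severe disease. Growth restriction is unlikely to arise between that moment and delivery. A fetal death or an abruption may have happened before she arrived or may happen afterwards. For a woman who presents postpartum, all three were settled before she came. The printed numerators add these groups together.

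This has two consequences. Events that precede arrival dilute any real effect, good or bad, towards no change. A shift in who arrives, through referral patterns or chance, also moves the rates when the protocol has done nothing, and it can offset a real harm or benefit. A larger sample would cure neither. The article offers these rates as safety information for later studies, so a reader could be wrongly reassured or wrongly alarmed.

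**Working it through.** The article gives no event rate, sample size or power for the fetal outcomes, so there is no figure to reproduce. What follows shows a range under stated assumptions.

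**Inputs**
- From the article: 4,500 to 5,000 deliveries a year (Study site); pre-eclampsia incidence in Ghana of 2.9% to 9.9% (Introduction); a three-month baseline (Study timeline).
- Assumed: *s*, the share of baseline events already present at arrival, at 20%, 50%, 80% and 100%.
- Assumed: *k*, the ratio of at-arrival prevalence, later period to baseline.
- Assumed: *R*, the true ratio for events that arise after arrival.

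**Formula**

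Observed ratio = s × k + (1 − s) × R, ignoring the small change in the number at risk when *k* differs from 1.

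**Step 1, dilution (k = 1).** For s = 50% and R = 0.5: 0.5 + 0.5 × 0.5 = 0.75.

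**Step 2, case-mix shift with no protocol effect (R = 1).** For s = 50% and a 30% fall at arrival: 0.5 × 0.7 + 0.5 = 0.85.

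**Step 3, masking.** Setting the observed ratio to 1 with R = 1.5 gives the fall in at-arrival prevalence that hides the harm completely: 1 − k = 0.5 × (1 − s) / s. For s = 80%: 0.5 × 0.2 / 0.8 = 12.5%.

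| s | True halving appears as | True doubling appears as | No effect, arrivals −30% / +30% | Fall at arrival that hides a 1.5-fold harm |
|---|---|---|---|---|
| 20% | 0.60 | 1.80 | 0.94 / 1.06 | 200%, so impossible |
| 50% | 0.75 | 1.50 | 0.85 / 1.15 | 50% |
| 80% | 0.90 | 1.20 | 0.76 / 1.24 | 12.5% |
| 100% | 1.00 | 1.00 | 0.70 / 1.30 | not applicable: no later events |

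**Step 4, size of the baseline.** The low end is 4,500 / 4 × 0.029 = 32.6 and the high end 5,000 / 4 × 0.099 = 123.8. That is about 33 to 124 pre-eclampsia cases of all severities in three months. It applies national incidence to hospital deliveries. A referral hospital may see more, and the severe subset is smaller. With numbers of this order, chance shifts in who arrives are plausible.

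**Step 5, after redefinition.** If only events arising after arrival are counted, among pregnancies at risk at arrival, the ratio measured is *R* itself, whatever *s* is, as long as some such events occur.

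**The case against.** The other side has a good deal to say, and much of it stands.

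- **A reader might infer that the fetal safety signal mostly reflects who arrives.** The article does not support this. It gives no share of fetal deaths or abruptions present at arrival, and the table runs from a minor distortion at 20% to a total one at 100%.
- **A reader might extend the point to every fetal outcome.** Neonatal ICU admission and Apgar score do not fit this mechanism for women who arrive undelivered. Preterm birth depends partly on when delivery follows arrival, so it is not fixed beforehand.
- **A reader might say the plan breaks its own rule, because "Patients who present dead on arrival to the emergency unit will be excluded".** The parallel is weak. That exclusion removes women who cannot receive the protocol at all. A woman who arrives with a fetal death is still eligible and treated.
- **Arrival data may well be collected.** The Data collection section draws presentation and case-mix data from emergency-unit records, and presenting diagnoses could reveal some fetal deaths or abruptions. A condensed article need not list every field, so a missing field is not the finding.
- **The stakes are limited.** The comparison is descriptive, the primary outcome is implementation success, and no decision rule described in the article uses these rates. Case-mix confounding also affects the other outcomes of an uncontrolled before-after comparison.

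The definitions themselves remain unanswered. Table 1 states explicit numerators and denominators, and the Secondary outcomes section points to it for the detail. Followed exactly, they pool the two kinds of event, and nothing in the article links the case-mix data to the fetal rates. Descriptive reporting lowers the consequence but does not make the rates interpretable.

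**Conclusion.** The point holds for three rates: intrauterine fetal death, placental abruption and growth restriction. As defined, a change in any of them between periods cannot be attributed to the protocol. The size is unknown because the share present at arrival is not given, and every ratio in the table is an illustration. Growth restriction is the clearest case; that rests on clinical reasoning about how quickly it develops, not on a figure in the article. For fetal death and abruption the distortion may be small or large.

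This is a modest but worthwhile correction to secondary, descriptive outcomes. It does not touch the primary outcome, and it does not show that the fetal safety information as a whole is uninformative.

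**What to change.** Record on the electronic case report form, at emergency-unit arrival: antepartum or postpartum status, fetal heart status, abruption status and gestational age. Then revise Table 1:

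- count intrauterine fetal death as an outcome only when it arises after arrival, among women who arrive undelivered with a live fetus;
- count abruption in the same way, among such women without abruption at arrival;
- report events present on arrival, and growth restriction, separately as case mix for each period;
- keep preterm birth as an outcome and show gestational age at arrival beside it.

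The Data collection section says the form is still to be developed and piloted, so the cost is a few fields plus revised definitions. No treatment changes. The price is fewer outcome events. Some pre-implementation records may also lack arrival findings; where they do, report the all-events rate alongside and state how many records are affected.

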#### Qualitative analysis

Perceptions of individual and behavioral factors influencing the implementation of the protocol will be analyzed thematically from the interview transcriptions. Ten clinicians (obstetricians, anaesthesiologists, intensivists, midwives, critical care nurses) who are involved in the care of this cohort of patients will be interviewed before and after the implementation of the protocol. Barriers and facilitators will be analyzed using the Consolidated Framework for Implementation Research (CFIR 2).^(36)^ The CFIR 2 is ideally suited to facilitating identification, coding, and synthesis of context-specific behaviors, perceptions, and beliefs that may influence implementation.

To ensure reliability, transcripts will be analyzed by two researchers independently under the direct supervision of two researchers, who have extensive experience as researchers. The transcripts will first be reviewed line by line to generate open codes. The codes will then be analyzed to create categories of related codes. Further analysis of the categories will yield themes mapped to the CFIR 2 framework. These themes would then be used as part of a complementary analysis in understanding the quantitative RE-AIM findings.

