### Objectives

First, this study will assess the feasibility and impact of implementing a clinician-co-designed and context-adapted protocol for managing patients with pre-eclampsia and eclampsia.

Secondly, the study aims to evaluate the potential impact of the protocol on clinical care processes and outcomes (including safety endpoints).

The study will identify barriers and facilitators to implementing a clinician-co-designed protocol for managing pre-eclampsia with severe features and eclampsia, as reported by healthcare professionals (doctors, Nurses/Midwives, and pharmacists), and report adaptations to the protocol design and implementation strategy to overcome these barriers. To achieve these aims, the study combines Medical Research Council (MRC) recommended guidance for stakeholder-led protocol development, with an implementation evaluation tool, the Reach, Effectiveness -Adoption Implementation and Maintenance (RE-AIM) framework.^(12)^

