### Implementation of the clinical protocol/guidelines

Once developed, the clinical protocol for the management of pre-eclampsia with severe features and eclampsia will be implemented in the clinical setting.

To improve the chances of implementation success, a combination of implementation strategies has been selected, given their superior effect in combination, when compared to the use of a single strategy.^(20)^ Strategies will include education, audit and feedback, and the use of local champions to guide implementation, adaptation, and tailoring. These strategies have been demonstrated to be feasible and effective in Lower- and Middle-Income Countries, but have not been evaluated in the context of emergency obstetric and maternal care in Ghana.^(21)^

A stakeholder is defined as any group or individual who is responsible for or affected by health- and healthcare-related decisions that can be informed by research evidence.^(22)^ In this study, the key stakeholders will be management members and clinicians (Obstetricians, Nurses/midwives, and Pharmacists). Extensive stakeholder engagement before an intervention can lead to a better understanding of barriers and local needs, ultimately improving the chances of successful implementation and adoption.^(23)^ The stakeholders will be informed about and educated on the project, its objectives, and the implementation plan.

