### Education

Education in implementation science ensures that key stakeholders have adequate knowledge and information about an intervention, thereby improving uptake.^(24)^ The newly adapted clinical protocol for the management of pre-eclampsia with severe features and eclampsia will be shared with all clinical professionals (Nurses/Midwives, Doctors, and Pharmacists) in the Directorate of Obstetrics and Gynecology of the Komfo Anokye Teaching Hospital to study. Subsequently, training will be organized for all clinical professionals directly involved in the care of this patient cohort, in groups of 20 - 30. During the training, participants will be taken through the protocol's objectives and benefits, their roles, and the implementation process. The training will be completed a week before the start of the protocol implementation.

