### Evaluation of implementation success/failure and impacts on clinical outcomes

The RE-AIM framework will be used to evaluate the implementation of the protocol intervention. RE-AIM framework offers a systematic evaluation of the effectiveness and impact of healthcare interventions. It is increasingly used both in Hybrid trials and to support implementation evaluations alongside more classical RCTs.^(12)^ In addition, interviews with stakeholders will be conducted prior to and following implementation. The interviews will explore stakeholder perceptions of protocolized care and identify behavioral factors that may influence implementation success. Interviews will be conducted by the research team, online, and de-identified, and transcribed prior to analysis.

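### The objective promises barriers and facilitators as reported by pharmacists, but the stated interview sample includes none, so that part of the objective has no planned formal data

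*Protocol article*

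**What the plan says.** Four sections of the protocol article bear directly on who reports barriers and facilitators.

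- **Objectives.** Barriers and facilitators are to be identified "as reported by healthcare professionals (doctors, Nurses/Midwives, and pharmacists").
- **Implementation of the clinical protocol/guidelines.** It states that "the key stakeholders will be management members and clinicians (Obstetricians, Nurses/midwives, and Pharmacists").
- **Evaluation of implementation success/failure and impacts on clinical outcomes.** It states that "interviews with stakeholders will be conducted prior to and following implementation", without listing professions.
- **Qualitative analysis.** The interviewees, seen before and after implementation, are "Ten clinicians (obstetricians, anaesthesiologists, intensivists, midwives, critical care nurses"). Perceptions "will be analyzed thematically from the interview transcriptions", and "Barriers and facilitators will be analyzed using the Consolidated Framework for Implementation Research (CFIR 2"). The themes then serve as a complementary analysis to help interpret the RE-AIM results.

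The Education section adds that the adapted clinical protocol "will be shared with all clinical professionals (Nurses/Midwives, Doctors, and Pharmacists") of the Directorate.

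**The concern.** The objective defines the barrier and facilitator findings by who reports them and names three professional groups. The sample that is to supply those reports draws on two. If the study is run as written, its report cannot present pharmacists' views on the same footing as those of doctors and nurses or midwives, although the objective promises this.

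Identifying barriers is a stated aim, and the Discussion calls it critical before wider scaling. The themes are also meant to help explain the RE-AIM findings. Fidelity is one of these, and its checklist includes the timeliness of magnesium sulfate administration. If fidelity falls below the 80% threshold, the formal interview data will hold nothing from a group that the article itself counts among its key stakeholders. Interviews that should precede implementation cannot be recovered once it has begun.

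**Working it through.** No formula applies and the plan gives no figure to reproduce. The check is a comparison of lists, followed by a search for any other section that closes the gap.

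**Step 1: objective against sample.**

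| Group in Objectives | Professions in Qualitative analysis | Covered? |
|---|---|---|
| Doctors | Obstetricians, anaesthesiologists, intensivists | Yes |
| Nurses/midwives | Midwives, critical care nurses | Yes |
| Pharmacists | None | No |

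Groups covered: 2 of 3. Pharmacists planned: 0 of 10 before implementation and 0 of 10 after. The bracketed list carries no wording that marks it as a set of examples, so it reads as complete.

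**Step 2: the general statement on interviews.** The Evaluation section says stakeholders are interviewed, and the Implementation section counts pharmacists among the key stakeholders. Together these imply that pharmacists are interviewed. The Qualitative analysis list therefore disagrees with this pair of sections as well as with the Objectives.

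**Step 3: other routes by which barriers are gathered.**

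- *Study timeline:* weekly meetings with clinical stakeholders during the six weeks of active implementation. No professions are named and no analysis is described.
- *Protocol selection and adaptation:* feedback from wider stakeholders at the drafting stage, before implementation. Again no professions and no analysis.
- *Implementation champion:* the champions who pass on colleagues' difficulties are a nurse or midwife and a doctor.
- *The study team:* the listed co-design team has no pharmacist.

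None of these supplies analysed pharmacist data. Every section that lists by profession the people who feed in information on barriers leaves pharmacists out.

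**Step 4: what adding pharmacists would displace.** The article gives no numbers per profession. If the ten were spread evenly over the five listed professions, each would have 10 / 5 = 2 interviewees per round. With pharmacists as a sixth profession and the total held at ten, the average would be 10 / 6 ≈ 1.7. The even spread is an assumption used only to show the scale of the trade-off.

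**The case against.** The strongest reply has four parts.

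1. *Most of the objective is covered.* This is right. Doctors and nurses or midwives are sampled, and the part of the objective about reporting adaptations to the protocol and strategy is untouched. A reader might infer that the plan cannot answer the objective at all. The documents do not support that.

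2. *Barriers are also collected outside the interviews.* This stands in part. Meetings, wider feedback and champions may bring pharmacists' difficulties to light, so it would be too strong to say that nothing from pharmacists could reach the team. These routes are informal, however, and the planned thematic analysis draws only on transcripts.

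3. *The consequences are easily overdrawn.* This also stands. A reader might infer that barriers in drug supply and dispensing would be missed, and that the secondary time-to-treatment outcomes would go unexplained. The article nowhere places such barriers with pharmacists, and it links the themes to the RE-AIM findings rather than to those secondary measures. The supported link is to fidelity. Nor does the article say that pharmacists are trained. The Education section shares the protocol with them, but describes training for professionals directly involved in this cohort's care without naming pharmacists.

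4. *This is a condensed article, and sampling detail often sits in the full protocol.* Silence would be excused on that ground. Here the article states both the sample size and the professions, and they differ from its own objective. The reply leaves some doubt over whether the list is exhaustive, but it does not remove the contradiction.

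**Conclusion.** The concern holds in a limited form. As written, one of the three professional groups in the objective has no planned formal data in either interview round, so the pharmacist part of the objective is unsupported. The Qualitative analysis list also conflicts with what the Implementation and Evaluation sections jointly imply.

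The computation of reach, fidelity and adoption, the 80% threshold and the secondary measures are not affected. What is affected is the scope of the qualitative conclusion and how far it can help explain the RE-AIM findings. This is a modest inconsistency, worth correcting because it is cheap to correct and because the pre-implementation round cannot be repeated later.

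The conclusion rests on two assumptions: that the bracketed list of professions is complete, as its wording suggests, and that no fuller document adds pharmacists to the interview sample.

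**What to change.** Reconcile the Objectives, Implementation, Evaluation and Qualitative analysis sections before the pre-implementation interviews, in one of two ways.

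- **Include pharmacists.** Name them among the ten interviewees in both rounds. The total number of interviews does not change. The cost is fewer interviews from the other professions. The article gives no basis for deriving how many pharmacists are needed, so the team should choose and state the number.
- **Narrow the claim.** Remove pharmacists from the barriers and facilitators objective, limit the conclusion to the professions interviewed, and say in the Evaluation section which stakeholders the interviews cover. This needs no extra data collection. The cost is that the study no longer claims to report the pharmacists' view.

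Either way the edit is small, about a sentence in each section concerned.
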